## 20 Study design

### 21 Type of study and design

All primary objectives and most exploratory objectives will be addressed through the conduct of a phase 4, randomized, controlled clinical vaccine trial. A total of 330 healthy children aged 24 – 59 months will be enrolled into one of three groups of equal size (3 x 110 children):

- (i) LAIV-vaccinated (Group A - blood sample at day 0, 2, 21)
- (ii) LAIV-vaccinated (Group B - blood sample at day 0, 7, 21)
- (iii) Control group (Group C)

Allocation concealment will be maintained from the start through the use of sealed envelopes. Block randomization stratified by sex will be used and a randomization sequence will be generated by an MRC Statistician not involved in the study. Investigators will not be blinded to group allocation from this point onwards as the sampling schedule differs between groups. Local laboratory staff will therefore not be blinded for this reason, but samples sent to external laboratories will be blinded (see section 3.2.3).

Two LAIV-vaccinated groups are included in order to achieve several exploratory objectives, which require blood sampling at different time points following vaccination, whilst minimizing the number of times children are bled times (i.e. 2nd blood sample at either day 3 or day 7 post-LAIV, but not both). The unvaccinated subjects will serve as a control group for the primary objective of assessing the impact of LAIV on the nasopharyngeal microbiome. Section 8 details the statistical considerations made to decide on the sample sizes to be recruited. The vaccination and sampling schedules for groups A, B and C are detailed in Tables 1.

Group C subjects will be administered LAIV after the NPS is taken on their day 21 visit, to offer them the same level of protection against influenza illness by participating in the study as those in groups A, B and D.

An additional 35 healthy children aged 24 – 59 months will be recruited in the 2nd phase of recruitment (Jan – June 2018) to assess the objective of how modulation of the nasopharyngeal microbiome with antibiotics impacts the mucosal immunogenicity to LAIV

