(Group D – vaccination and sampling schedule in Table 2), by administration of a single dose of oral azithromycin 28 days prior to receiving LAIV. This timeframe has been chosen based on pilot data from the the Gambia showing significant alternation in the nasopharyngeal microbiome approximately 1 month after single dose oral azithromycin in Gambian children aged 1 – 7 years in mass trachoma treatment campaigns ([name], unpublished, personal communication). These subjects will be matched as closely as possible by pre-antibiotic nasopharyngeal microbiome profile [1], age (24 – 35, 36 – 47, 48 – 59 months) and sex (in that hierarchical preference), in a nested case-control study, to n = 35 children recruited in the main clinical trial. This will be done after all children have been recruited and microbiome sequencing and analysis has been completed. To avoid allocation bias of these controls, an individual in the [name] laboratory blinded to the immunogenicity data will undertake this matching process. In brief, the microbiome profile matching will be performed by first categorizing which of eight described profiles each child's microbiome clusters with depending on the dominant taxa (e.g. *Staphylococcus*, *Streptococcus*, *Moraxella* etc.) as described previously by the [name] group [1].

The day 2 visit window for groups A, B and D is deliberately restrictive to allow both blood and NPS to be taken at a time when peak gene expression changes post-LAIV can be captured. The other visit windows are intentionally liberal to maximize the opportunity to obtain a full set of blood and NPS samples for the purpose of the analysis, whilst in each case, not compromising the scientific objectives they are designed to deliver. However, in each case, the intention will be to obtain the sample on or as close to the day specified as possible. The sampling schedule and associated laboratory assays to be performed on each clinical sample is detailed in Table 3. The procedure to deal with participants who default visit windows is discussed in section 5.4.

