Participants in groups A and B (n = 110 each) will be enrolled for approximately 4 –10 months: 21 days of active participation during recruitment months January – June 2017 or January – June 2018, followed by attendance at the Sukuta Health Centre for assessment of any ILI that occurs up to the 31st of October in the year of recruitment into the study. This design has been chosen as data from Senegal show that peak influenza transmission occurs between July and October each year ([name], XVII International Symposium on Respiratory Viral Infections, Vancouver, CA, 2015).

Group C will be enrolled for 21 days, with participation finishing following the day 21 visit and receipt of LAIV (Table 1). Group D (n = 35) will be enrolled for approximately 4 – 10 months: 49 days of active participation during recruitment months January – June 2018, followed by attendance at the Sukuta Health Centre for assessment of any ILI that occurs up to 31.10.18. Those individuals presenting with possible ILI will have a limited history taken and if a sudden onset of a fever of  $\geq 38^{\circ}\text{C}$  (axillary) *and* either a cough or sore throat is present, a nasopharyngeal swab will be taken and diagnostic viral rRT-PCR performed.

The vaccine to be studied (Nasovac-S) has a WHO pre-qualification certificate and marketing authorization for the study population. However, the trial will provide detailed information on the determinants of immunogenicity and therefore inform the design of future generations of similar live intranasal influenza vaccines.

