## 22 Allocation concealment, randomization and blinding procedures

### 23 Allocation concealment and randomization

Following informed consent, subjects will be assigned a unique subject identification number (section 3.2.2) and details recorded on an enrollment log. If eligibility is confirmed according to the defined inclusion and exclusion criteria (section 5.3), children will be randomized into one of the three equally sized groups as defined in section 3.1 above (for groups A, B and C).

Randomization will be undertaken using pre-prepared, sealed opaque envelopes to maintain allocation concealment. Block randomization stratified by sex will be undertaken using a computer generated randomization sequence pre-prepared by an individual not otherwise involved in the study or its analysis. The block size and randomization sequence will not be known by any member of the investigator team, hence ensuring allocation bias is avoided. Information regarding the group into which a participant has been randomized will be revealed to the team only when opening the envelope.

At the time of randomization, the person undertaking randomization will take the next envelope in numerical sequence. The randomization list will be cross-checked by a second individual both of whom will be required to sign to document the process.

The 35 subjects for group D will be recruited sequentially after recruitment in groups A, B and C have been completed, during the 2nd recruitment season (January – June 2018).

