#### **40 Administration**

The investigator, or designee, will be responsible for the preparation and administration of study vaccines to study participants according to the procedures in the study protocol and/or Study Specific Procedures (SSPs). All vaccines will be administered only by a study clinician or nurse who is qualified and trained to perform this function.

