## **57 Withdrawal and discontinuation of subjects**

If after signing of the informed consent form, the investigator ascertains that the subject does not fulfill all criteria for study entry, the case report form (CRF) pages need not be completed. Only the reason for subject exclusion should be noted on the screening log. Data on screening failures will therefore be collected.

If a subject who does not fulfill all criteria for study entry is inadvertently deemed eligible and included in the trial (either randomized in the case of Groups A, B and C or given azithromycin in group D), the investigator must terminate the subject's participation in the trial. If the subject

was randomized and administered the study vaccine, the subject should be followed for safety for 21 days following administration of Nasovac-S, if possible. However, no further samples will be taken from the subject and the data will be excluded from the analysis.

A parent/guardian may withdraw a child from the study at any time without giving a reason. This will not in any way affect their care otherwise. A parent/guardian may either withdraw from further participation only (in which case all clinical samples and data obtained prior to withdrawal will be evaluated as part of the study) or withdraw from further participation *and* from the use of any clinical data/samples already collected. If the latter option is requested by the parent/guardian of the child, collected samples will be destroyed, a request made for data withdrawal and this process documented. Irrespectively, the clinical trial team will make all reasonable efforts to monitor, follow-up and when necessary treat adverse events under such circumstances according to the procedures outlined for this trial (see section 7).

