### **75 Final confirmation of eligibility and definition of enrolment**

Eligibility for enrolment will be confirmed on the basis of the above (Section 6.1.3). A child will only be defined as being enrolled in the trial once final confirmation of eligibility has been determined and randomization has occurred.

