#### **117**    Pause rules

As there is robust safety data on the study vaccine Nasovac-S, as well as azithromycin, this study does not have any defined safety endpoints. However, the occurrence of any SUSAR will always result in a pause in recruitment. An evaluation will be made on whether the risk-benefit balance of the study has changed in light of the SUSAR. The decision on whether to continue the trial will be made by the sponsor, taking into account the information provided by the PI, the local safety monitor, the manufacturer (SIIL) and if necessary external experts (e.g. pharmacists). The sponsor's representative will collect all data and consult with MRC (the sponsor) head office prior to a decision being made.

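### After a SUSAR only recruitment pauses automatically; LAIV doses still due in enrolled Group C and Group D children are held only by discretion until the sponsor decides

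*Combined protocol and SAP*

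**What the plan says.** Section 117 notes the established safety record of both products, then makes one action mandatory: "However, the occurrence of any SUSAR will always result in a pause in recruitment". A risk-benefit evaluation follows, and the sponsor decides whether the trial continues. No deadline is given. Section 118 (Study discontinuation) is also framed around ongoing recruitment.

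The protocol treats recruitment as an entry event. Section 51 bounds the recruitment periods by first and last subject first visits. Section 75 says: "A child will only be defined as being enrolled in the trial once final confirmation of eligibility has been determined and randomization has occurred". Section 57 fixes the moment of inclusion as "either randomized in the case of Groups A, B and C or given azithromycin in group D".

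Two groups receive LAIV after that moment:

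- **Group C** is vaccinated at the day 21 visit (+7 days, Table 1), after its last swab, "to offer them the same level of protection against influenza illness by participating in the study". Section 21 describes the group as enrolled for 21 days, "with participation finishing following the day 21 visit and receipt of LAIV".
- **Group D** is defined "by administration of a single dose of oral azithromycin 28 days prior to receiving LAIV" (day 0 visit +7 days, Table 2). Section 23 adds: "The 35 subjects for group D will be recruited sequentially after recruitment in groups A, B and C have been completed".

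**The concern.** The pause is mandatory so that risk and benefit are reassessed before more children are exposed. As worded, that automatic protection covers children who have not yet entered. It does not cover healthy children already in the trial who are waiting for the same vaccine.

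In most single-dose vaccine trials, stopping entry stops dosing. Here that holds only for Groups A and B. Once Group D recruitment starts, no child receives LAIV at entry, so a recruitment pause stops no LAIV dose due in the next 28 days. After recruitment closes it stops none at all.

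Group C is the clearest case. Its dose is not needed for the microbiome comparison it was recruited for. After the dose there are 30 minutes of observation (section 82) and no scheduled safety visit (section 108).

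**Working it through.** **Inputs.** Section 51: season 1 target 195 (65 in Group C); season 2 target 170 (45 in Group C, 35 in Group D); recruitment January–June, which is 181 days or 25.86 weeks. Tables 1 and 2: wait from entry to LAIV of 21–28 days in Group C and 28–35 days in Group D.

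**The plan's own rate.** 195/6 = 32.5 and 170/6 = 28.3 per month, rounding up to the stated 33 and 29. With four-week months the weekly rates are 195/24 = 8.1 and 170/24 = 7.1, matching the stated 7–8. By calendar weeks they are 195/25.86 = 7.54 and 170/25.86 = 6.57.

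**Children waiting = weekly rate × weeks from entry to LAIV** (steady accrual).

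| Group C | per week | 3 weeks | 4 weeks |
|---|---|---|---|
| Season 1: 65/25.86 | 2.51 | 7.5 | 10.1 |
| Season 2, A–C at overall rate: 6.57/3 | 2.19 | 6.6 | 8.8 |
| Season 2, A–C filling the season: 45/25.86 | 1.74 | 5.2 | 7.0 |

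This gives about 5–10. The number is lower in the first three weeks of a season and zero between seasons.

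| Group D at recruitment close (cap 35) | 4 weeks | 5 weeks |
|---|---|---|
| 6.57 per week | 26.3 | 32.9 |
| 7 per week | 28 | 35 |
| 8 per week | 32 | 35 |
| 35 over 8 weeks (4.38 per week) | 17.5 | 21.9 |
| 35 over 13 weeks (2.69 per week) | 10.8 | 13.5 |

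The protocol gives no accrual rate specific to Group D, so the last two rows are an assumed slow case. At 6.57 per week recruitment closes on 30 June 2018 and the last doses fall between 28 July and 4 August, after there is any recruitment left to pause.

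**Doses due during a pause.** The length is assumed; 7 and 15 days are borrowed from the reporting limits in section 115. Group C: 1.74–2.51 per week gives 1.7–2.5 in 7 days and 3.7–5.4 in 15. Group D at 6.57 per week, while its day 0 visits run: 6.6 and 14.1.

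**Chance of a SUSAR.** The frequency is not given. An assumed 1 in 10,000 to 1 in 1,000 gives 1 − (1 − p)^365 = 3.6% to 30.6% over all 365 children. Section 8 reports no related serious event in 7,565 recipients of the same manufacturer's earlier monovalent vaccine. The 95% upper bound is about 3/7,565 = 0.0004, which gives about 13.5%. That evidence is indirect, but it makes the top of the assumed range look too high.

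**Chance at the Group D peak.** At 6.57 per week Group D recruitment lasts 35/6.57 = 5.3 weeks (37 days), so Groups A and B were last dosed more than 21 days before it closes. Take 21 days as the risk window (assumed, from the adverse event collection period in section 108).

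- On-time visits: 35 − 26.3 = 8.7 Group D children dosed, plus Group C doses over about 4.7 days at 2.19 per week (1.5), total about 10.
- Full windows: 35 − 32.9 = 2.1, plus about 11.7 days of Group C doses (3.7), total about 6.

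At the assumed frequencies the chance is 6 × 0.0001 = 0.06% to 10 × 0.001 = 1%.

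**Group D data at risk from a hold.** Windows lapsing in a pause of T days = (T − 7) × 6.57/7, for on-time visits.

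- No attrition: the margin from 35 to the 30 in section 121 is 5, reached at T = 7 + 5 × 7/6.57 = 12.3 days.
- With the 10% attrition in section 51: 31.5 remain, the margin is 1.5 and the rate is 0.9 × 6.57 = 5.92 per week, so T = 7 + 1.5 × 7/5.92 = 8.8 days.

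**The case against.** The strongest reply is that nobody would keep vaccinating while a SUSAR is under review. Section 40 says: "The investigator, or designee, will be responsible for the preparation and administration of study vaccines to study participants". Willingness is confirmed at each visit (section 69). Serious events reach the sponsor and local safety monitor within 24 hours (section 115). Deviations to remove an immediate hazard are allowed (section 141). The trial is bound to GCP and the Declaration of Helsinki (section 154), and consent is repeated when new information is judged relevant (section 160). Children keep access to medical care until 31 October (sections 83 and 108). The vaccine is WHO-prequalified, and Group C's dose may protect before the July–October season.

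All of this stands, and it limits the point. A reader might infer that enrolled children have no protection, or that the protocol requires dosing to go on. The documents support neither: the provisions listed permit or prompt a hold. But none orders one, and section 117 chose an automatic rule over discretion for recruitment.

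The objection on size also stands. A reader might take the 145 of 365 children whose LAIV is separated from entry (110 + 35, 40%) as the number exposed at one SUSAR, or combine the whole-trial chance with the Group D peak. The first is a cumulative count. The peak is brief and coincides with few recent vaccinations.

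**Conclusion.** The gap holds as a matter of wording, and only for the interim: once made, the sponsor's decision on continuing the trial covers every pending dose. Until then, the children affected are about 5–10 in Group C during steady recruitment. In Group D the peak is about 26–35 if it accrues at the overall planned rate, or about 11–18 with on-time visits if recruitment takes 8–13 weeks. These are doses waiting, not doses certain to be given, and attrition would lower them. The counts rest on even accrual at the section 51 targets. The probability of a SUSAR cannot be taken from the documents and is likely to be low. Minor to should-fix: the event is improbable, but a mandatory pause exists for improbable events and the correction is cheap.

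**What to change.** Amend section 117 so that any SUSAR pauses recruitment and all further LAIV administration, expressly including Group C day 21 and Group D day 0 doses, until the sponsor's decision. Group C's day 21 swab is still taken on schedule.

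Add a rule for a +7 day window that lapses when the trial continues. Section 58 does not settle this, because Group C has no later visit and Group D's later visits are timed from LAIV.

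- **Group C:** give LAIV later.
- **Group D:** offer LAIV later and exclude the child from the post-LAIV azithromycin comparison. Keep the day-28 post-azithromycin swab, which needs no LAIV.

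Aligning the recruitment wording in section 118 is optional.

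Cost: Group C loses no swab data, but its vaccine benefit may be delayed. In Group D, a pause longer than about 9 days with 10% attrition (about 12 without) could take the exploratory microarray comparison in section 121 below 30, in children who had already received an antibiotic they did not need for their own health (section 157). Sample size and power for the primary objectives are unchanged.

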#### **118**    Study discontinuation

Study discontinuation could occur following the assessment of the conditions related to a given pause rule being activated such that ongoing recruitment was no longer judged to be appropriate for any reason (see section 7.7). Also, if further information, external to the trial, becomes available (e.g. though newly published literature) which is considered to alter the safety profile of the trial such that it is no longer justified.

### **119**    Statistical considerations

#### **120**    Sample size

Sample size calculations have been considered with relation to the three main primary objectives in the study (section 2.1.1).

#### **121**    Identifying novel early systemic and mucosal signatures following LAIV that are associated with robust nasal and oral influenza-specific IgA responses

A precise power calculation is difficult to perform as a number of markers will be studied in an unbiased analysis, rather than testing whether a single defined marker is associated with vaccine endpoints. Microarrays will be performed (peripheral blood and NPS-derived RNA) on a subset of children at the opposite ends of the IgA response spectrum following LAIV (n = 30 in each group), thus identifying those at the extremes of response. A further 30 children, given azithromycin, will also have microarrays performed at baseline and day 2 following LAIV and results compared to n = 30 age, sex and baseline microbiome profile-matched children.

[name] has successfully identified markers of vaccine immunogenicity in cohorts of

similar or smaller sizes than those proposed following several vaccines including LAIV, IIV, yellow fever and polysaccharide-based meningococcal vaccines [66, 67, 71]. Over 2000 genes were differentially expressed at day 3 post-LAIV when compared to baseline [66].

Although there are no data in Gambian children given LAIV to use in sample size calculations, estimates can be provided based on microarray data from healthy Gambian children (2 – 59 months) recruited as controls in a pneumonia study ([name], unpublished data), which is the best available data to use. The *ssize* package [72] in R was used to estimate the number of children required to identify differentially expressed genes between two groups. Using the strict Bonferroni correction to adjust for multiple testing, 30 subjects in each group is required to ensure that at least 90% of genes (of 49,386) have a power of  $\geq 90\%$  at  $\alpha 0.01$  to detect a 2-fold change (see Figure 1 below). Using the more relaxed false discovery rate to control for multiple testing, 10 subjects in each group would be sufficient.

[figure not shown]

**Figure 1. Sample size estimates to detect 2-fold gene expression changes**

## 122 Identifying associations between nasopharyngeal microbiota and nasal and oral influenza-specific IgA responses post-LAIV in Gambian children, to explore whether microbiome variability can explain suboptimal immune responses in some individuals

Calculations were performed using the Shiny application for determining sample size calculations for case-control microbiome studies (<https://fedematt.shinyapps.io/shinyMB/>) [73]. Simulations were run using the anterior nares-derived microbiome data available on the application, estimating that analyses would consider the most abundant 150 operational taxonomic units (OTUs). IgA responders and non-responders were defined as cases and controls respectively and sample size/power calculations performed to detect a 1.5-fold

difference in abundance in the 10 most abundant OTUs and 2-fold difference in abundance in the next 10 most abundant OTUs, between the two groups (Figure 2).

Power calculations were performed using these parameters, for a range of sample sizes from 50 – 150 per group and using the Wilcoxon-Mann-Whitney (WMW) test applied to each OTU individually and the resulting *P*-values multiplicity adjusted with the Benjamini and Hochberg method to control the false discovery rate ('WMWavg' – Figure 3). Prior data suggest that approximately 50% of children receiving LAIV are IgA responders, using a definition of  $\geq 2$ -fold rise in IgA from baseline [7]. At an alpha of 0.05, 82 subjects per group would give a power of 80%. A sample size of  $n = 100$  per group was selected (i.e.  $n = 200$  children given LAIV, accounting for approximately 50% showing an IgA response), which even accounting for some drop outs would give a power of  $\geq 80\%$ .

If required, the complexity of data may be reduced by defining microbiota composition according to 8 distinct profiles described by the [name] group [1] rather than variability across 20 different OTUs/species, thus reducing the need for correction for multiple testing and increasing the power significantly.

[figure not shown]

**Figure 2. Simulations of anterior nares derived microbiome data showing differences between cases and controls of the 20 most abundant OTUs.**

[figure not shown]

**Figure 3. Sample size and power estimates to detect differences in the top 20 most abundant OTUs between two groups (1.5-fold difference in the top 10 abundant OTUs and 2-fold difference in the next 10 most abundant OTUs). WMWavg refers to the Wilcoxon-Mann-Whitney test as applied to each OTU and multiplicity adjusted to control for false discovery rate.**

